### Interventions

The strategy comprises an Internet-based platform developed as a social network tailored to health professionals’ use that allows the sharing of patients’ information, documents, and treatment plans between the hospital and 18 PCUs. In addition, telemedicine support will be made available for patients who, for any reason, do not receive specialist services. An electronic knowledge platform will also be developed to keep the health professionals updated through a distance-learning course (DLC) in clinical management focused on diseases that are part of the Brazilian ACSC list.Communication platformsAn Internet-based social network that was developed using free software (based on the open source project Hubzilla [17], formerly known as Redmatrix) and was tailored for this intervention will be made available to the HMMD and PCU health teams [18]. This platform will host private communications among the health providers about their common patients. This shared information will flow through secure channels using the HTTP Secure (HTTPS) protocol to ensure that patients’ information can only be accessed by the appropriate health professionals, whose identity will be authenticated by their credentials (login and password).The platform’s interface includes a hospitalization alert that will ask for specific information that can help the hospital teams to manage the patient during their stay. The responses from the PCU will be incorporated into the hospital electronic medical record. Afterwards, the discharge summary and prescriptions will be delivered to the PCU through a similar discharge alert. Beyond the sharing of information, each alert allows for an online asynchronous conversation to develop between the professionals at each end.Additionally, a telemedicine service (already implemented at HMMD) will be made available to those patients followed during the study, who, for any reason, do not reach specialized services in the SUS. For example, long waiting times for consultations or more sophisticated exams, patient’s lack of resources to pay for transportation to the point of care, or simply absenteeism are situations that can hinder treatment plans, potentially harming patients’ clinical outcomes. Eligible patients will be referred by the primary care teams. These patients will then visit HMMD, where they will be seen by an HIAE physician or nurse specialist via telemedicine equipment. This is an ongoing project supported by the HIAE and the Ministry of Health, with benefits reported among patients seen in the HMMD emergency room [19].Clinical management updating DLCA DLC based on the Brazilian ACSC criteria, focusing on physicians, nurses, and multi-professional staff, will be implemented. The DLC will be hosted by the HIAE Teaching Department’s structured platform, Taleo™. This knowledge platform was conceived to transmit and record web conferences, host discussion forums, and store and transfer archives. Other educational resources, such as structured clinical cases, will be developed to illustrate situations faced by health providers in real-world scenarios.The DLC will be divided into five modules, each 8 weeks in duration, covering the Brazilian ACSC list: respiratory, cardiovascular, diabetes, gastroenterology and mixed infectious diseases, and major health risk factors (smoking, alcoholism, drugs, pain, nutrition, and physical inactivity). Web conferences will be transmitted and recorded on a weekly basis. The 18 PCUs and HMMD will participate in the web conferences, which will feature a presentation on an ACSC by a professional expert speaker and a professional generalist’s comments on specific issues to provide participants with updated evidence-based knowledge. A tutor will encourage discussions in the forum, using a structured clinical case as a tool to demonstrate the applicability of the scientific evidence. The use of the ACSC-related guidelines and/or of evidence-based protocols will be emphasized. After each module, a face-to-face meeting will be carried out to emphasize teamwork and clinical decision-making processes, wrapping up the module content with mixed discussion groups tasked with generating proposals from the health providers for applying evidence-based recommendations at their care facilities. The DLC participants will be evaluated based on their participation in the discussion forums, weekly quizzes, and a final exam at the end of each module. Additionally, the participants will use a structured questionnaire to evaluate each module in terms of their satisfaction with the DLC structure, content, relevance to clinical practice, and feasibility of application in the workplace [see Additional file 1].

### Sample and study design for impact evaluation

PatientsThe impact evaluation of the integration strategy will use a quasi-experimental cohort with historical controls design. Participants will be adult patients hospitalized for ACSC who will be followed up 1 year after their hospital discharge. Patients’ data will be compared with data on the same patients from different time periods as historical controls, using medical records dating at least 1 year before and 1 year after the patients’ inclusion in the study.The sample of patients will be selected in two stages. First, a convenience sample of 18 PCUs will be selected, as described above. In the second stage, 560 hospitalized adult patients living in the territories covered by and registered in the selected PCUs will be selected based upon their main or secondary diagnosis, which must fit the Brazilian ACSC criteria, excluding female pelvic disorders and pregnancy-related diseases (Table 2). The calculation of this sample size was based on the 2013–2014 HMMD incidence of 30-day readmissions for ACSC, which was 16 %. This sample size will permit a valid logistic model with up to nine covariates to be fit [20].

**Table 2 Tab2:** Diagnoses included in this study and their International Classification of Diseases (ICD-10) codes

Diagnosis	ICD-10 code
Infectious gastroenteritis and complications	E86, A00–A09
Gastrointestinal ulcer	K25–K28, K92.0, K92.1, K92.2
Ear, nose, and throat infections	H66, J00–J03, J06, J31
Bacterial pneumonias	J13–J14, J15.3–J15.4, J15.8–J15.9, J18.1
Diseases of the lower airways	J20, J21, J40–J44, J47
Asthma	J45–J46
Tuberculosis	A15.4–A15.9, A16.3–A16.9, A17.1–A17.9
Pulmonary tuberculosis	A15.0–A15.3, A16.0–A16.2
Heart failure	I50, J81
Hypertension	I10–I11
Angina pectoris	I20, I24
Cerebrovascular diseases	I63–I67, I69, G45–G46
Diabetes mellitus	E10–E14
Infection in the kidney and urinary tract	N10–N12, N30, N34, N39.0
Epilepsies	G40–G41
Syphilis	A51–A53
Infection of the skin and subcutaneous tissue	L01, L02, L03, L04Exclusion criteria are being under palliative care or dying during the first hospitalization, as well as being unable to respond to the questionnaires because of a cognitive deficit or an unstable clinical condition. The data of all eligible ACSC patients identified by the research team will be analyzed according to their diagnosis, length of stay, outcomes (discharge, death, or transfer to another hospital), and readmission rates.The Brazilian validated version of the Primary Care Attention Tool [21], the World Health Organization Quality of Life (WHOQoL Brief) [22], and a sociodemographic questionnaire [see Additional file 2] developed by the research team based on other validated instruments [23–27] to collect data on social and environmental characteristics will all be administered at the bedside after the patient has signed the informed consent form, and again at the follow-up visit in the patient’s home or PCU, as chosen by the patient. At the follow-up, an additional questionnaire about treatment plan adherence [see Additional file 3], disease monitoring, and access to all levels of the health services will also be administered.Data on the selected patients will be gathered from their medical records and the electronic system of the São Paulo Municipality (SIGA SAÚDE), which registers all patient visits to the points of care managed by the São Paulo municipal health system, as well as prescribed medications. From both HMMD and the PCUs, medical record data will be collected covering the time period at least 1 year before and 1 year after hospitalization, following the historical control design chosen for this study, to search for evidence related to the number of consultations, health promotion and education actions, and access to the other levels of the SUS. Several telemedicine-related variables will also be collected: the reason for the consultation, diagnostic or therapeutic aid, information use in decision making, and patient’s obtained outcomes. All data collected by the research team will be submitted to an inter-rater reliability analysis using Gwet’s coefficient [28].At the follow-up visit, some interviews will be video recorded, for patients who authorize the use of their images, to obtain additional information that will be analyzed qualitatively about their use, personal impressions, and satisfaction with the health system. All interviews will be transcribed and coded through subsequent qualitative analysis, informed by the discourse of the collective subject theory [29]. All of the participating patients’ addresses will be mapped using the free software and open data service Open Street Map [30] assess correlations between social and environmental vulnerabilities and patient’s health status.

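### For consultations and access to care, the same-patient year-before versus year-after comparison cannot separate the effect of the hospital admission from the effect of the platform and course

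*Protocol article*

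**What the plan says.** Under Sample and study design for impact evaluation, the protocol article describes a quasi-experimental cohort. Its comparator is "data on the same patients from different time periods as historical controls". The windows are at least one year on each side of the patient's entry into the study. Entry is tied to an admission for an ambulatory care sensitive condition (ACSC): "Participants will be adult patients hospitalized for ACSC who will be followed up 1 year after their hospital discharge". Consent and baseline questionnaires are obtained at the bedside.

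The same section applies this design to service use. For the hospital and the primary care units (PCUs), "medical record data will be collected covering the time period at least 1 year before and 1 year after hospitalization", and the purpose is "to search for evidence related to the number of consultations, health promotion and education actions, and access to the other levels of the SUS".

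Table 1 shows how the results will be read. Objective 4 is to establish the longer-term impact of the two strategies by following this cohort, and access to health services is listed among its main outcomes. The Data analysis plan names generalized linear models and generalized estimating equations for comparisons over time. Study status dates the course from July 2014 to July 2015 and patient inclusion from November 2014 to March 2016. It says the platform is fully implemented but gives no start date.

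**The concern.** A before/after comparison within patients is informative about an intervention if nothing else that matters changes at the split. Here something does: the split is the index hospitalization, and it is there for every patient by construction.

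An admission can change later service use in several ways.

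- Discharge can prompt return visits and referrals.
- Some Table 2 conditions, for example "Cerebrovascular diseases", may be recognised for the first time at the admission.
- Visits may cluster in the weeks before an admission, which inflates the before-year.
- Everyone survived the before-year, but deaths cut some after-years short.

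The first two push the contrast up and the last two push it down. None depends on whether the platform or the course existed. At stake is whether a change in consultations or access, in either direction or none, may be reported under Objective 4 as the impact of the strategies.

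**Working it through.** **1. The plan's own figure.** The cohort size rests on 30-day readmission (16%) and up to nine covariates. The article does not state the rule; ten events per covariate is inferred. N = 10 × 9 / 0.16 = 562.5, against the stated 560. At 560, expected events are 560 × 0.16 = 89.6, or 89.6 / 9 = 9.96 per covariate. The figure reproduces, and this point does not affect it.

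**2. What the contrast identifies.** Write the after/before ratio of mean consultations as R = a × s × t. Here a is the effect of the admission, s the effect of the strategies and t the average fraction of the after-year lived. The cohort gives R. Counting per time alive deals with t. Nothing in the cohort separates a from s, because after the admission and after the split are the same indicator for every patient. For the course, the spread of admission dates does not help: inclusion began four months after the course started, so no cohort member has an after-year that predates it.

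**3. Does the split mark exposure?** Measure months from 1 July 2014. Inclusion runs from m = 4 (1 November 2014) to m = 21 (31 March 2016). The share of the before-year falling after the course began is min(m, 12) / 12.

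- Smallest value: 4 / 12 = 33%, for the earliest patients.
- Mean under uniform accrual (an assumption): [(12² − 4²) / 24 + (21 − 12)] / 17 = (5.33 + 9) / 17 = 0.843, about 84%.
- Patients whose before-year lies wholly after the course start: (21 − 12) / 17 = 53%.

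Suppose the course multiplied visits by 1.25 from its start onward (an assumption), with nothing else changing. The before-year mean would already be raised by 1 + 0.843 × 0.25 = 1.211, and the contrast would show 1.25 / 1.211 = 1.03. For the course, the split can therefore hide a real effect as well as create a false one.

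**4. How easily a false effect appears.** The documents give no consultation rates, so every rate here is assumed. The simulation had 560 patients, Poisson counts before and after with gamma (shape 1) patient frailty, no intervention effect, a paired two-sided t-test at 5%, and 1,000 runs per setting. Newly diagnosed patients were given half the usual rate in the before-year.

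| Admission effect assumed | 2 visits/yr | 4 visits/yr | 8 visits/yr |
|---|---|---|---|
| None | 5.6% | 3.9% | 4.5% |
| Follow-up raises visits 10% | 64% | 89% | 99.6% |
| Follow-up raises visits 25% | 99.9% | 100% | 100% |
| 10% newly diagnosed, no follow-up rise | 22% | 36% | 57% |
| 30% newly diagnosed, no follow-up rise | 95% | 99% | 100% |

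Cells show the percentage of studies with a significant before/after difference. Only upward effects were simulated. A run-up before admission, or deaths in raw counts, would act the other way. The table shows that a small admission effect is enough; it does not predict which sign will be seen.

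**The case against.** Five arguments stand on the other side.

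- *Splitting at admission has a rationale.* The platform works through an admission alert and a discharge alert, and better PCU follow-up after discharge is what it is meant to produce. So not every post-discharge rise is artefact. This stands, but it restates the problem: intended effect and ordinary follow-up occur in the same window, and no group shows ordinary follow-up alone.
- *The article admits the limitation.* The Discussion concedes difficulty in isolating intervention effects and says the study is mainly about implementation. The concession is generic. It neither names this mechanism nor changes the comparison or the wording of Objective 4.
- *Objective 3 supplies calendar-time data.* It covers ACSC admissions from 2013 to 2017, but from hospital records, and so does not measure PCU consultations or access.
- *Direction and size are unknown.* This stands. A reader might infer that consultations are bound to rise, perhaps to double, with no intervention effect. The documents do not support that: they give no visit rates and no share of new-onset disease. Table 2 also contains many acute infections and long-standing conditions, and two of the mechanisms lower the contrast.
- *Only secondary outcomes are concerned.* This also stands. The primary outcome is 30-day readmission, and Table 1 gives the main analysis for Objective 4 in terms of readmission rates.

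**Conclusion.** The point holds in a limited form. For consultations and access to other levels of care, the plan's own definition of the historical control places the admission at the split for every patient. The effect of the admission and the effect of the strategies are then inseparable, and no model fitted to this cohort alone can recover the difference. This follows from the design text and needs no assumed rates.

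The size is not known. Under the stated assumptions, a 10% change caused by the admission is enough to give a significant result in most studies. The split also fails to mark exposure to the course: at least 33% of every before-year falls after the course began, and about 84% on average if accrual was uniform. The corresponding figure for the platform cannot be computed, because its start date is not given.

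The consequence is a possible wrong attribution in secondary results. The sample size and the primary outcome are not called into question here.

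**What to change.** **Minimum change, in the Patients part of Sample and study design for impact evaluation.** State that the same-patient before/after change in consultations and access is descriptive and is not evidence of the impact of the strategies. Report these outcomes as rates per time alive. This costs a few sentences and an offset in the model.

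**For any impact statement.** Compare the year after discharge in the cohort with the year after discharge in ACSC patients of the same 18 PCUs discharged January to June 2013. Their after-year ends by 30 June 2014, before the course began. Use the SIGA SAÚDE visit data, apply the cohort's exclusions as far as records allow, and adjust for diagnosis group and age. Do not subtract each group's before-year: most of the cohort's before-year is already exposed to the course, so a difference of changes would cancel part of any real course effect. First confirm that the platform was not in use from January 2013 to June 2014.

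**Cost and limits.** This adds a record extraction, with whatever ethics approval it needs, and no new visits or patients. Calendar-time differences remain, including changes in recording from the Lean Six Sigma project and the telemedicine service begun in April 2016. The earlier group has no questionnaires, and its ability to answer them can only be approximated from records. Health promotion and education actions are not covered, because the article does not say that SIGA SAÚDE records them; for those the comparison should stay descriptive.

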### Patients’ medical records

To ensure the quality of the data that will be gathered from the medical records, a sub-project will be carried out using the Lean and Six Sigma techniques to improve the quality of the information registered by the health providers. The Lean Six Sigma approach has been used to aggregate value in different processes, reducing waste and adding more uniformity and precision through the application of statistical tools [33, 34]. These principles have been recommended for application in clinical and translational research [35]. This project will be focused on the health records review boards of HMMD and the PCUs, and it will be carried on in partnership with the Process Improvement Department of the HIAE. Requirements for the quality criteria for information in the medical records will be defined and aligned as part of the study, to be audited by the members of these review boards. Additionally, inter-rater reliability analyses will be conducted among the auditors on a regular basis.

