### Study status

At this time, the Internet-based platform has been fully implemented. The DLC was conducted from July 2014 to July 2015. All data related to the health providers have been collected. The Lean Six Sigma project was completed in March 2016. The patients’ selection and inclusion began in November 2014 and was completed in March 2016. Patient follow-up visits are underway. The telemedicine consultations began in April 2016.

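### Before/after counts taken from hospital and PCU charts overlap a study project that improves charting, so part of any rise in these secondary counts may reflect documentation and not care

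*Protocol article*

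**What the plan says.** Under Sample and study design for impact evaluation, each patient is his or her own control: "Patients’ data will be compared with data on the same patients from different time periods as historical controls". No concurrent group is described. For HMMD and the PCUs, "medical record data will be collected covering the time period at least 1 year before and 1 year after hospitalization", and the stated purpose is "to search for evidence related to the number of consultations, health promotion and education actions, and access to the other levels of the SUS". Table 1 (Objective 4) adds that the PCU records are on paper.

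The section on patients' medical records describes a sub-project "using the Lean and Six Sigma techniques to improve the quality of the information registered by the health providers". It covers both sites of data collection: "This project will be focused on the health records review boards of HMMD and the PCUs". Study status gives its end: "The Lean Six Sigma project was completed in March 2016". Its start is not given. The same section says patient inclusion ran from November 2014 to March 2016.

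Two other sources bear on the point. Patient data also come from SIGA SAÚDE, "which registers all patient visits to the points of care managed by the São Paulo municipal health system". Table 1 also plans audits of record content, with adequacy compared over time by chi-square tests.

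**The concern.** The chart is the measuring instrument for both sides of an uncontrolled before/after comparison, and the study itself sets out to change that instrument during the evaluation. If providers write down a larger share of what they do, the recorded number of actions rises even when care is constant. The bias favours the after-period, which is also the direction the platform and the course are expected to act in, and there is no comparison group in which to see it.

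Health-promotion and education actions are the most exposed, because the article names no second source for them. Consultations and access are less exposed, because SIGA SAÚDE is also collected, but the sentence that lists these counts ties them to HMMD and PCU records and does not say which source governs. The record audits would measure the drift, yet nothing in the article links them to the counts. At stake are the secondary service-use conclusions of Objective 4.

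**Working it through.** **The plan's own figure.** The 560 is justified by 16% readmission and up to nine covariates. At 10 events per covariate (a rule inferred here; the article gives no formula), 9 × 10 / 0.16 = 562.5, close to 560. Expected events are 560 × 0.16 = 89.6, or 9.96 per covariate. This figure concerns readmission and is not in dispute.

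**Inputs from the article.** Inclusion lasts 17 months (November 2014 to March 2016). The project ends at month 17. Windows are at least 12 months each side, taken here as 12. n = 560, and the significance level is 5% (taken as two-sided).

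**Assumptions, none of them in the article.** Inclusion is uniform. True care is unchanged at μ = 4 actions per patient-year. The charts capture a share c0 = 0.70 of actions before the recording change and c1 = 0.75, 0.80 or 0.85 after it. Variation is Poisson. The change takes effect at one month s.

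**Step 1: share of each window under improved recording.** For a patient included at month t and s = 17, the exposed share of the after-window is (t − 5)/12 for t above 5, and zero otherwise. Averaged over 17 months this is (12²/2)/(12 × 17) = 35%; the before-share is 0%. The first 5 of 17 inclusion months, about 29% of patients, have no exposed after-time. For s = 11, the before-share is (6²/2)/(12 × 17) = 9% and the after-share is 1 − (11²/2)/(12 × 17) = 70%.

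| Recording change takes effect | Before-time exposed | After-time exposed |
|---|---|---|
| Project completion (month 17) | 0% | 35% |
| Month 11 | 9% | 70% |
| Month 9 | 16% | 80% |
| Month 5 | 35% | 94% |
| Start of inclusion (month 0) | 65% | 100% |

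The after-window is the more exposed in every row.

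**Step 2: spurious ratio with no change in care.** Average capture is p0 = c0 + (c1 − c0) × before-share and p1 = c0 + (c1 − c0) × after-share. The ratio is p1/p0.

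**Step 3: chance of a significant difference.** z = μ(p1 − p0) / √(μ(p0 + p1)/560), and the rejection probability is Φ(z − 1.96) plus a negligible or small lower tail.

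| Change | c1 | p0 | p1 | Ratio | z | False-positive rate |
|---|---|---|---|---|---|---|
| Completion | 0.75 | 0.700 | 0.718 | 1.03 | 0.70 | 11% |
| Completion | 0.80 | 0.700 | 0.735 | 1.05 | 1.39 | 29% |
| Completion | 0.85 | 0.700 | 0.753 | 1.08 | 2.08 | 55% |
| Month 11 | 0.75 | 0.704 | 0.735 | 1.04 | 1.21 | 23% |
| Month 11 | 0.80 | 0.709 | 0.770 | 1.09 | 2.39 | 67% |
| Month 11 | 0.85 | 0.713 | 0.805 | 1.13 | 3.54 | 94% |

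**Step 4: sensitivity.** An overdispersion factor of 2 divides z by √2. At completion the rates become 8%, 17% and 31%; at month 11 they run from 14% to 71%. Halving μ to 2 has the same effect on z. The ratios do not change.

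**The case against.** A reader might infer that every before-year was recorded the old way and every after-year the new way. Ratios would then be 0.75/0.70 = 1.07, 0.80/0.70 = 1.14 and 0.85/0.70 = 1.21, with false-positive rates at 4 actions per year of about 50%, 97% and over 99%. The dates in Study status do not support that. If the change came at completion, patients included before about April 2015 have after-windows that closed before it; if it came earlier, it reaches into the before-windows too.

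Further points on the other side are fair:

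- The article speaks of the quality of registered information and not of its completeness. A fuller note need not add a consultation to the count. A rise in capture is an inference. It is reasonable for education actions, which may go unwritten, and weaker for consultations.
- SIGA SAÚDE is already a source, the follow-up questionnaire covers access to services, and the audits track record adequacy. It is therefore too strong to say that documentation and care cannot be separated. What stands is that the article does not use these sources to separate them.
- Table 1 ties the Objective 4 models over time to readmission, and the article says only that evidence on these counts will be sought. It does not follow that a rise will be read as better care; it may be.
- The Discussion admits limits in isolating intervention effects. It does not name this one.

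The choice of source for a secondary count is often left to a fuller document. Here, however, two stated design choices work against each other, which is more than an omitted detail.

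**Conclusion.** The concern holds for secondary outcomes. As described, chart-derived counts are biased toward the after-period. Under the stated assumptions the spurious rise is about 3–8% if recording changed at project completion and about 4–13% if it changed 11 months into inclusion. The matching false-positive rates are about 11–55% and 23–94% against a nominal 5%, and lower with overdispersion or fewer actions per year.

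The direction rests on the dates and on the inference that better registration raises capture. The size rests on capture shares, onset, action rate and variance, none of which the article gives, so the figures are illustrations and not estimates. The 30-day readmission outcome and its sample size are outside this point.

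**What to change.** 1. Make SIGA SAÚDE the main source for before/after visit counts in both windows, for municipally managed points of care. State that it does not cover care outside them, and confirm that the record-quality project did not alter entry into it, since the article does not say.
2. Report chart-derived health-promotion and education counts, and any access measure SIGA SAÚDE cannot supply, as sensitive to documentation and not as stand-alone evidence of impact.
3. For those counts, add a sensitivity analysis by calendar time relative to the record-quality project, whose start date should be stated, and by the audited record adequacy already planned in Table 1.
4. Name this bias among the limitations.

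The cost is some extra analysis and wording, using sources already being collected while follow-up is under way. The real loss is that the chart-only outcomes give up their claim as evidence of impact.
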